**Methods:**

A total of 132 FSWs will be recruited and randomly assigned to either the intervention or usual care (control) groups in a multi-centred randomised controlled trial. Based on the resilience framework, this intervention is comprised of six weekly sessions focused on the awareness, expression and management of emotions, identifying roles and personal strengths, and effective problem-solving skills. Complex intervention assessment on both intervention process and effectiveness will be adopted when the primary outcome reduction of sexual risk behaviour and other psychological outcomes include their perceived stress, self-esteem, self-efficacy, coping overall resilience, and psychological distress will be measured at baseline, post-treatment and 3-month post-intervention and differences assessed by ANOVA. The relationship of resilience factors, psychological health and HIV preventive behaviours will be evaluated using structural equation modelling.

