#### Research aims and objectives

The Personal Resilience and Enrichment Programme (PREP) has been developed according to resilience framework for a trial with FSWs in Hong Kong. The aim of this study is to seek a new direction for HIV prevention by investigating the effectiveness of PREP in FSWs. Through promoting FSW psychological health, it is hypothesised FSWs will take better care of their physical well-being and actively practise HIV preventive measures, and hence reduce their HIV risks. Specifically, the objectives of this study include:

1. To evaluate the effectiveness of PREP, the resilience-promoting intervention, in enhancing FSWs’ overall resilience, reducing their psychological distress, and eventually reducing HIV risk behaviours among FSWs in Hong Kong.

2. To explore the mechanism of how individual resilience factors operate to promote better psychological outcomes and decreasing HIV infection among FSWs.

This study is a randomised controlled trial to test the hypothesis that the participants in intervention group, as compared to those in the control group receiving usual care, would have an improvement in HIV preventive behaviour through the increase in overall resilience and in terms of their self-efficacy, self-esteem and coping strategies. At the same time, it is hypothesised that this cohort of FSWs’ psychological distress would be reduced upon completion of the programme and such improvements would be continued at least in the 3-month post-intervention period. The study will further explore the operation of the resilience model by specifying the association of stress perceived by FSWs, and the effects of the resilience attributes (self-esteem, self-efficacy, and coping strategies) on their level of psychological health and HIV preventive behaviours (Figure 1).

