## Methods & design

### Study design

This is a randomised controlled trial in which participants will be randomly assigned to either intervention group or usual care as the control group. Participants in the intervention condition will receive the 6-session PREP, whereas participants in the control group will receive usual care. Outcome measures of all participants will be collected at baseline, completion of intervention or 6 to 12 weeks after baseline for control group, and 3 months thereafter.

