#### Generalized self-efficacy scale

This scale contains 10 items to assess the strength of individual’s belief in their own abilities to respond to difficult situation [49,50]. Items are rated on a 4-point Likert scale, with a high total score indicating a high level of general self-efficacy. Sample item includes “I can always manage to solve difficult problems if I try hard enough”. The internal consistency (alpha = 0.86) and test-retest reliability (r = 0.75) of the original scale have been shown to be satisfactory (alpha = 0.86). The Chinese version of the scale used in the present study has demonstrated satisfactory internal consistency (alpha = 0.86).

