### Data analyses

First of all, the baseline demographics of the intervention and control groups will be compared with independent sample *t*-tests for continuous variables and *chi*-square for categorical variables to assess the compatibility of the two-trial arms at baseline to ensure both groups were similar to start with. The change of scores on sexual health risks and psychological outcome measures (self-esteem, self-efficacy, coping, resilience and GHQ) over time between two groups will be analysed using analysis of variance with intention-to-treat analysis. Bivariate correlation analyses will be performed to examine the relationship between psychological variables and behavioural outcomes. Linear regressions will also be used to examine the associations and the effects of resilience, self-esteem, self-efficacy, coping on psychological health outcomes and HIV preventive behaviours. The statistical analyses will use SPSS 20.0 and *p*-values of 0.05 or less will be considered statistically significant.

The second objective of the current study is to explore the mechanism of how individual resilience factors influence the psychological outcomes and HIV preventive behaviours in FSWs (as proposed in Figure 1). Structural equation modelling (SEM) identifies connection strengths that best predict the observed structure of the data with respect to the specified model. Thus, SEM will be performed to evaluate the model fit of the proposed model that links psychological resources with harm-reduction behaviours as measured by condom use.

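### The psychological scales are compared as change scores by ANOVA; the planned test is valid, but adjusting for each scale's baseline score would be more precise at almost no cost.

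*Protocol article*

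**What the plan says.** The Data analyses section names the quantity to be compared: "The change of scores on sexual health risks and psychological outcome measures (self-esteem, self-efficacy, coping, resilience and GHQ". For the method, it then states that these changes "over time between two groups will be analysed using analysis of variance with intention-to-treat analysis". The abstract agrees: outcomes "will be measured at baseline, post-treatment and 3-month post-intervention and differences assessed by ANOVA".

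The Study design section confirms that the baseline values will exist: "Outcome measures of all participants will be collected at baseline", again at the end of the intervention (6 to 12 weeks after baseline for controls), and 3 months after that.

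The only other use of baseline data in comparing the arms is a set of t-tests and chi-square tests on demographics, "to assess the compatibility of the two-trial arms at baseline to ensure both groups were similar to start with". No adjustment follows from them. The linear regressions and the structural equation model described in the same section concern associations and mechanism, not a baseline-adjusted effect of arm.

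The scales are listed under Secondary outcome measures. They still carry the first part of objective 1, which is to evaluate PREP "in enhancing FSWs’ overall resilience, reducing their psychological distress, and eventually reducing HIV risk behaviours among FSWs in Hong Kong".

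**The concern.** A change score uses the baseline by subtracting it whole, which fixes the slope of follow-up on baseline at 1. With equal SDs at the two visits the actual slope is the correlation rho, which is below 1. Subtracting too much baseline has two effects. It adds noise, so intervals are wider than they need be. It also ties the estimate to whatever baseline difference chance produces: the arm that starts higher tends to show the smaller gain.

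Reading the method as a repeated-measures ANOVA does not remove this, because baseline then enters as one more outcome visit and still not as a covariate. With a single follow-up, the group-by-time test is the change-score comparison.

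At stake is precision on resilience and distress, the first link in the trial's proposed chain from PREP to condom use. The sample size was set on condom use alone, so power on the scales was not planned for.

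**Working it through.** **The plan's own figure.** The Sample size section gives 66 per group from a 49.3% rate, a 25% difference, 80% power and two-sided 0.05. Taking 25% as percentage points (49.3% against 74.3%, mean 61.8%):
- Uncorrected: n = [1.96·√(2·0.618·0.382) + 0.8416·√(0.493·0.507 + 0.743·0.257)]² / 0.25² = 58.1, rounded up to 59.
- With continuity correction: (58.1/4)·[1 + √(1 + 4/(58.1·0.25))]² = 65.9, rounded up to 66.

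The stated 66 reproduces. It concerns the binary outcome and serves here only as the number per arm.

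**Inputs for the scales**
- n = 66 per arm (Sample size), taken as completers with independent observations.
- Two-sided alpha 0.05.
- Correlation over the trial interval: not given. The nearest figures are test-retest values of 0.90 for the Chinese 10-item Connor-Davidson scale and 0.75 for the original self-efficacy scale ("test-retest reliability (r = 0.75) of the original scale have been shown to be satisfactory"). A value of 0.5 is added as an assumption.
- Equal SDs at all visits, set to 1, with the same correlation between any two visits.

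**One follow-up visit**
- Change-score variance factor: 2(1−rho).
- Baseline-adjusted variance factor: 1−rho².
- Ratio, adjusted to change score: (1+rho)/2.
- Noncentrality: (n/2)d² divided by the variance factor. The effect d is chosen so that the change score has 80% power (noncentrality 7.97), and the adjusted noncentrality is 7.97/ratio.

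| rho | d (SD) | variance ratio | CI width ratio (square root) | power, change score | power, adjusted |
|---|---|---|---|---|---|
| 0.90 | 0.220 | 0.950 | 0.975 | 80% | 82% |
| 0.75 | 0.347 | 0.875 | 0.935 | 80% | 85% |
| 0.50 (assumed) | 0.491 | 0.750 | 0.866 | 80% | 90% |

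A simulation at rho 0.5 (4000 runs, 66 per arm, true effect 0.40 SD) gave standard errors of 0.174 for the change score and 0.153 with adjustment. The variance ratio is (0.153/0.174)² = 0.77, against 0.75 in theory. The mean estimate was 0.406 for both methods, so neither shows bias.

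**Dependence on a chance baseline difference**
- SD of the chance difference: √(2/66) = 0.174 scale SDs, so 0.2 SD is an ordinary size.
- The change-score estimate moves by (1−rho) times the difference, in the opposite direction: 0.25·0.2 = 0.05 SD at rho 0.75, and 0.5·0.2 = 0.10 SD at rho 0.5.
- In the simulation the change-score estimate correlated −0.49 with the baseline difference, and the adjusted estimate 0.01.

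**If the ANOVA is a three-visit group-by-time test.** Assume equal effects at both follow-ups and 80% power for the 2-df test, with noncentrality (n/2)(2/3)d²/(1−rho) on 2 and 260 df.
- The 1-df contrast of the follow-up mean minus baseline has variance factor (1+rho)/2 + 1 − 2rho = 1.5(1−rho). Its noncentrality equals that of the 2-df test (9.75), and its power is 87% at every rho.
- Adjusting the follow-up mean for baseline has variance factor (1+rho)/2 − rho²: 0.14, 0.3125 and 0.50 at rho 0.90, 0.75 and 0.50, against 0.15, 0.375 and 0.75 for the contrast. Power is 89%, 92% and 97%.

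The covariate alone therefore adds about 2, 5 and 9 points. The step from 80% to 87% comes from using one degree of freedom and is not a benefit of adjustment.

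**The case against.** The strongest reply is that the planned analysis is sound. Averaged over randomisation, the change-score estimate is unbiased and its type I error is not inflated. A reader might infer from the dependence on baseline that the psychological results would be biased. The documents do not support that: the shift is conditional on a chance imbalance and averages to zero. This reply stands, and it makes the point one of efficiency.

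Second, the correlations that the article does give imply small gains: 2 points of power for resilience and 5 for self-efficacy. This also stands, with one qualification. Test-retest values are best read as an upper guide, because follow-up comes 6 to 12 weeks after baseline and then 3 months later, and the programme is meant to change these scores. A lower correlation and a larger gain are plausible, but the 10-point gain remains an assumed case.

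Third, the scales are secondary. Adjusting them leaves the condom-use comparison and its sample size untouched. The power figures are also idealised: the Limitations section anticipates drop-out among controls, and the intervention is delivered in groups of 3 to 6. Both are correct, and they set the weight of the point.

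Fourth, a condensed article names only a family of methods, and a covariate could appear in an unseen plan. This is weaker, because the text does more than stay silent: it names the change of scores as the quantity compared.

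A reader might also suppose that the baseline t-tests and chi-square tests will be used to choose covariates. Nothing in the article says so; they are described only as a check of similarity.

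**Conclusion.** The point holds as an efficiency point on secondary outcomes that objective 1 names. The stated analysis is valid but discards precision that the collected baseline scores would supply. Adjustment cuts the variance by 5% at rho 0.90, 12.5% at 0.75 and 25% at an assumed 0.50. It also removes the estimate's dependence on a chance baseline difference.

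The sizes rest on equal SDs, 66 completers per arm, independent observations and a correlation that the article does not report for the trial interval. The direction does not depend on the value of rho: under equal SDs the ratio (1+rho)/2 is below 1 for every rho below 1. The point gives no ground for calling the planned comparison biased or its p-values wrong, and it does not touch the binary condom-use outcome.

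**What to change.** For each psychological scale, replace the change-score ANOVA with one of two models, chosen in advance: ANCOVA of the follow-up score on arm with that scale's own baseline score as covariate, or a mixed model over both follow-ups with the same baseline covariate. Report the adjusted mean difference with its 95% CI.

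The cost is a sentence in the analysis section and one degree of freedom per model. No extra data, visits or participants are needed, and SPSS 20.0, the package the protocol names, can fit these models. A missing baseline score needs a stated rule, as it already does under a change score.

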### Sample size

Sample size estimation is based on the “always” use condom rate during commercial transactions in the last month at 49.3% from the latest local study published on the topic [16] and an assumption of effect size of 25% on condom use rate between the intervention and control groups from a previous study [43]. In order to detect such a difference with a power of 80% and a two-tailed significance of 0.05, the sample size required is 66 in each group.

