### Usual care

Participants who are assigned to the control group will receive the standard service provision currently provided by the NGOs. Currently, the two local NGOs offer regular outreach visits and voluntary HIV/ STIs screening. Some FSWs also choose to join activities organised by the NGOs (e.g. yoga, English class or gathering). For this study, the usual service provision includes outreach visits made by the NGOs (usually the same venue will be visited once to twice a month), attending HIV/STI screening, and social activities according to their own needs and schedule. The nature of these contacts initiated by the outreach workers or sex worker themselves will be recorded. They will be advised not to join any additional psychological programmes during the study period or they have to leave the trial.

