### Limitations

Participants who volunteer for the study are arguably biased towards being more motivated and health-conscious but the design of randomised control trial equalises this effect in both groups. Furthermore there is the potential for the participants to have psychological distress and therefore screening by a clinical psychologist will help exclude those who are clinically depressed and need intensive treatment. Although the outreach staff will contact the FSW recruited regularly, the attrition rate of those who are motivated but assigned to the usual care group may be diminished and hence a potential tendency to drop out from the study. The aims and objectives of the study will be clearly explained to the potential participants and the “buy-in” will be sought before they agree to participate. Given Hong Kong is effectively one large metropolis and there are considerable overlaps between the two targeted NGOs, therefore, cluster randomised control trial will not be feasible. Even though the participants recruited from the two NGOs would be told specifically not to disclose, there may still be a risk of contamination between the intervention and control group given the participants may know each other.

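### Unless missed visits are imputed, the three-visit ANOVA uses only women with complete visits, which does not match its intention-to-treat label

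*Protocol article*

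**What the plan says.** The Data analyses section states that change in sexual health risks and in the psychological measures "over time between two groups will be analysed using analysis of variance with intention-to-treat analysis". It adds that "The statistical analyses will use SPSS 20.0". The abstract says the outcomes "will be measured at baseline, post-treatment and 3-month post-intervention and differences assessed by ANOVA". Study design sets the visits at baseline, then "completion of intervention or 6 to 12 weeks after baseline for control group, and 3 months thereafter". So there are three assessments per woman, one method (ANOVA) and one analysis principle (intention-to-treat).

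Two other places bear on who will be missing. Limitations, in a sentence whose wording is garbled but whose sense is clear, says of women who are motivated but allocated to control that the position of those "assigned to the usual care group may be diminished and hence a potential tendency to drop out from the study". Usual care says that control women will be "advised not to join any additional psychological programmes during the study period or they have to leave the trial".

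The article does not say that the ANOVA is a repeated-measures one, does not mention deletion of incomplete cases, and does not restrict the analysis to completers.

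**The concern.** The natural reading of change over time between two groups, with three visits, is a group-by-time ANOVA. In its classical form, as in the general linear model procedure of the named package, each woman must have a value at every visit, and a woman who misses one contributes nothing. Intention-to-treat promises that women are analysed as randomised. Once visits are missed, the method and the label agree only if something is added, such as imputation before the ANOVA.

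Two things are at stake. The first is precision: information already collected from women with one missed visit is thrown away. The second is comparability: if the two arms lose different kinds of women, the women who remain are no longer the randomised groups. The sentence covers sexual health risks, so the primary condom-use outcome is affected as well as the scales.

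**Working it through.** **1. The plan's own figure.** Inputs from Sample size: "use condom rate during commercial transactions in the last month at 49.3" per cent; "an assumption of effect size of 25% on condom use rate between the intervention and control groups"; 80% power; two-sided 0.05; 66 per group. Read as 25 percentage points, p1 = 0.493, p2 = 0.743 and the mean is 0.618.

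- n = [1.960 × √(2 × 0.618 × 0.382) + 0.842 × √(0.493 × 0.507 + 0.743 × 0.257)]² / 0.25² = [1.960 × 0.6871 + 0.842 × 0.6640]² / 0.0625 = 58.1, i.e. 59 per arm.
- With continuity correction: (58.1 / 4) × [1 + √(1 + 4 / (58.1 × 0.25))]² = 65.9, i.e. 66 per arm.

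The stated 66 is reproduced exactly. It contains no addition for dropout beyond whatever slack the continuity correction gives.

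**2. How many women have all three visits.** The article gives no loss rate, so these rates are assumptions. If each follow-up is missed independently with probability m, complete cases = 132 × (1 − m)².

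- m = 5%: 119
- m = 10%: 107
- m = 15%: 95
- m = 20%: 84

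If 10% miss the second visit and 20% the third, the complete fraction lies between 0.9 × 0.8 = 72% (independent) and 80% (nested), or 48 to 53 of 66 per arm.

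**3. Power if only complete cases count.** For n per arm, power = Φ[(0.25 × √n − 1.960 × 0.6871) / 0.6640], with no continuity correction.

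- No loss, n = 66: 84.9%
- 10% loss, n = 59.4: 80.9%
- 20% loss, n = 52.8: 76.0%
- 30% loss, n = 46.2: 70.2%

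With unequal loss (10% PREP with 20% or 30% control), the same test with unequal arm sizes gives 78.6% or 75.7%. These figures are for a single comparison of two proportions, which is what the sample size was built on. They are not the power of the group-by-time ANOVA.

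**4. Direction of bias.** Suppose there is no true effect (49.3% in both arms) and only controls are lost, a fraction d of them, with always-use rate q among the lost. The rate among remaining controls is (0.493 − d × q) / (1 − d). The apparent difference, PREP minus control, is:

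| d | q = 30% | q = 70% |
|---|---|---|
| 10% | −2.1 points | +2.3 points |
| 20% | −4.8 points | +5.2 points |
| 30% | −8.3 points | +8.9 points |

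Example: d = 20%, q = 70% gives (0.493 − 0.140) / 0.80 = 0.441, a gap of 5.2 points. The sign depends wholly on q, which the article does not give.

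Bias is not automatic either. A simulation used a continuous score with equal correlation between visits, 10% random loss in PREP, and control loss depending on the second-visit score. It gave mean bias of about zero and rejection rates of 4.5% to 5.7%. That setting is unbiased by construction, so it shows only that harm depends on why women leave.

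**5. A simple rule that would not help.** Counting missing as not always using, with no true effect and assumed loss of 10% in PREP and 20% in control, gives 0.493 × 0.90 = 44.4% against 0.493 × 0.80 = 39.4%. That is a spurious gap of 4.9 points in favour of PREP (0.493 × 0.10). At 10% and 30% loss the gap is 9.9 points.

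**The case against.** The strongest reply is that the conflict is inferred. The article never says repeated-measures or listwise deletion. Imputing before the ANOVA would satisfy both halves of the sentence, and comparing change visit by visit would omit only the women missing that visit. A condensed article commonly leaves such rules to the full protocol or analysis plan. All of this stands: the absence of a missing-data rule is not the point made here, and the point has to be conditional. What remains is that the one method the article fixes does not, on its own, deliver the population named in the same sentence.

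A reader might infer that the method and the label can never both hold, that the plan predicts heavy control dropout, or that motivated controls will leave and make PREP look better. The documents support none of these. Imputation would reconcile the two; Limitations speaks only of a potential tendency, gives no rate, and is accompanied by regular outreach contact and efforts to secure commitment beforehand; and nothing links motivation for PREP to condom use, so the bias could have either sign or be absent.

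It can also be said that a mixed model rests on missing-at-random and that motivation is not among the listed measures, so the model need not remove arm-related bias. That is correct, and it is why a sensitivity analysis is part of the fix. Nor would a mixed model restore the full 84.9% power: it recovers information from women with partial data but cannot replace outcomes never observed.

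**Conclusion.** The point holds in conditional form. Without imputation, ANOVA over three visits analyses women with complete visits only, which conflicts with the intention-to-treat label in a trial whose own Limitations foresee possible dropout in the usual-care arm. The rule about leaving the trial in Usual care is a further route to missing data.

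On assumed losses of 10% to 30% per arm, power for the planned difference falls from 84.9% to between 80.9% and 70.2%, crossing below the planned 80% somewhere between 10% and 20% loss. Possible bias under no effect reaches about 8 to 9 points in either direction at 30% control-only loss, if the lost women's always-use rate is 30% or 70%. Loss rates and lost women's rates are all assumptions. The figure of 66 per group is not in error.

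**What to change.** In Data analyses, replace the ANOVA sentence by:

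- **Scales:** a likelihood-based mixed model with arm, visit and their interaction, analysing women as randomised, using every available visit and accounting for baseline.
- **Binary condom outcome:** a mixed logistic model, or GEE after multiple imputation, on the same principle.
- **Sensitivity analysis:** vary the assumed outcomes of missing women separately in each arm and in both directions, including scenarios unfavourable to PREP. Do not rely on the single rule that missing means not always using, since it favours PREP whenever controls are lost more often.

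If the ANOVA is kept, the plan should state that missed visits are imputed first and how.

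The cost is a change of wording and slightly more analysis work with methods available in standard software; no extra data are needed. The price in assumptions is that the main model relies on missing-at-random, which the sensitivity analysis then tests.
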